### Safety Monitoring

The safety population is defined as all randomized participants who received at least 1 dose of the study intervention or were allocated to the control group and underwent at least 1 postbaseline visit. This population will be used for all safety analyses, regardless of protocol adherence, study completion status, or parental consent to laboratory investigations. Adverse events will be actively monitored at every study visit through symptom inquiry from parents or guardians, physical examination (temperature, pulse, respiratory rate, abdominal examination, and anthropometric measurements), review of concomitant medications, and laboratory assessments in a small group of participants. Laboratory investigations will also be conducted when there is a clear clinical need, rather than routinely for all participants. Specifically, if a child shows signs of liver disease, such as jaundice, LFTs will be performed within 48 to 72 hours after discussing the need for testing with parents. Similarly, for suspected kidney problems, such as reduced urine output, hematuria, or swelling, RFTs will be performed within the same time frame. If there are suspected blood-related issues, such as pallor or bleeding, a CBC and coagulation profile will be performed within 24 to 48 hours. For suspected metabolic or endocrine effects, tests such as fasting glucose, electrolytes, or thyroid function tests may be performed within 72 hours, depending on the symptoms. For a small group of willing participants, baseline and week 12 laboratory tests, including CBC, erythrocyte sedimentation rate, LFT, RFT, and serum electrolytes, will be performed, with separate consent obtained from parents. In all cases, parents will be fully informed about the necessity of the tests, and their concerns will be addressed to ensure they are comfortable with the process.

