## Methods

### Trial Design

The study is planned as a multicenter, open, randomized controlled, 2-group pilot study designed to investigate the therapeutic efficacy and safety profile of *Ayush-BR Leham* in managing moderate malnutrition in children aged 3 to 5 years. After obtaining written informed consent from the parents, the participants fulfilling the inclusion criteria will be randomized and assigned to the study and control groups in a 1:1 ratio. Both the study and control groups will be administered *Aravindasava* for 4 weeks to provide an initial correction of digestive function. Then, for a period of 8 weeks, *Ayush-BR Leham* will be administered to the study group, and the control group will be followed without any intervention. Both groups will undergo a follow-up period of 4 weeks. Throughout the study, both groups will be advised to strictly follow a home-prepared diet. The study protocol is reported in accordance with the SPIRIT (Standard Protocol Items: Recommendations for Interventional Trials) guidelines. The flowchart of the study plan is shown in Figure 1 [11].

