### Interventions

The drug *Aravindasava* has been procured from Indian Medicines Pharmaceutical Corporation Limited, a Good Manufacturing Practice–certified pharmaceutical company in Almora, Uttarakhand, with a quality assurance certificate ensuring compliance with the Ayurveda Pharmacopoeia of India standards [12]. The trial drug *Ayush-BR Leham* was prepared at the pharmacy of the Central Ayurveda Research Institute, Kolkata, as per the standard operating procedures developed by the Central Council for Research in Ayurvedic Sciences (CCRAS). The study drugs will be stored in a dark, cool, and dry place. The investigators will administer *Aravindasava* in both groups for 4 weeks at a dose of 5 mL twice daily after food, followed by *Ayush-BR Avaleha* in the study group at a dose of 5 g twice daily before food for 8 weeks. There will be no intervention in the control group after *Aravindasava* administration.

Both groups receive *Aravindasava*, ensuring that no group is disadvantaged in the early, critical phase, during which correction of digestion, absorption, and assimilation is necessary. All participants will receive standard nutritional care and public health interventions available to the general pediatric population with malnutrition during the study period. These include regular nutritional counseling by Accredited Social Health Activist workers or *Anganwadi* workers through government initiatives, age-appropriate dietary guidance from the study pediatrician, health check-ups and monitoring by the research team, management of infectious diseases that develop during the study, immunization, and routine health care. Both groups are advised to follow a home-prepared diet throughout the study. A home-prepared diet refers to age-appropriate, nutrient-dense meals that the family provides at home following personalized dietary counseling by the study team. It represents optimized nutrition within the family’s resources and cultural context. Compliance with the home-prepared diet will be recorded in the case report form (CRF).

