### Outcome Measures

The primary outcome measure is the proportion of participants attaining a change in the weight-for-age *Z* score (WAZ) by ≥0.5, as per WHO reference standards, from baseline to weeks 12 and 16. The secondary outcome measures include changes in anthropometric measurements (weight in kg, height in cm, and midupper arm circumference in cm), which will be assessed every 2 weeks for 12 weeks, followed by assessment at week 16. Change in the frequency of illnesses will be assessed at baseline, week 12, and week 16 using a predesigned table that records the frequency and duration of illnesses. Assessment of safety (complete blood count [CBC], liver function test [LFT], renal function test [RFT], and serum electrolytes) will also be performed at baseline and week 12 in a small proportion of participants whose parents provide consent.

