#### Follow-Up Assessments

All participants will undergo follow-up assessments on days 14, 28, 42, 56, 70, 84, and 112. Concomitant medication, rescue medication, drug compliance, and adverse drug reactions or adverse drug events will be assessed during the follow-up visits. Laboratory investigations will be performed at the day 84 visit for those who underwent baseline laboratory assessments (Table 1).

**Table 1 table1:** Study schedule.

Assessments	Screening or baseline	Follow-up		
		Weeks 2-10 (days 14, 28, 42, 56, and 70)	Week 12 (day 84)	Week 16 (day 112)
Informed consent from parent	✓			
Laboratory investigations (for those who are willing)	✓		✓	
Demographic characteristics and medical history	✓			
Weight-for-age *Z* score	✓		✓	✓
Anthropometric measurements (weight, height, midupper arm circumference, and BMI)	✓	✓	✓	✓
Assessment of illness frequency	✓		✓	✓
*Dosha*, *dhatu*, and *srotopareeksha* assessment	✓			
Assessment of concomitant medications		✓	✓	✓
Assessment of rescue medications		✓	✓	✓
Assessment of adverse drug reactions and adverse events		✓	✓	✓
Drug compliance assessment		✓	✓	
Dispensing of trial drug and compliance reporting form	✓	✓		

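### The safety population is defined differently by arm and does not say which product counts as the study intervention, so who enters depends on the reading, and one reading favours Leham

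*Protocol article*

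**What the plan says.** Under Safety Monitoring, the safety population is all randomised children who "received at least 1 dose of the study intervention or were allocated to the control group and underwent at least 1 postbaseline visit". The same section adds: "This population will be used for all safety analyses, regardless of protocol adherence, study completion status, or parental consent to laboratory investigations".

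Treatment is described under Trial Design ("Both the study and control groups will be administered" Aravindasava) and under Interventions, where Aravindasava is given to both groups "for 4 weeks at a dose of 5 mL twice daily after food, followed by" Leham in the study group only. For controls, "There will be no intervention in the control group after" Aravindasava.

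On data collection, Safety Monitoring says: "Adverse events will be actively monitored at every study visit". Follow-Up Assessments says: "All participants will undergo follow-up assessments on days 14, 28, 42, 56, 70, 84, and 112". Scheduled laboratory safety tests are done at baseline and week 12 "in a small proportion of participants whose parents provide consent" (Outcome Measures).

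Participant Withdrawal Guidelines lists serious adverse events, adverse drug reactions that require discontinuation, acute illness needing inpatient care and drug compliance below 80% among the reasons for withdrawal. A final examination follows only where possible.

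**The concern.** Safety of Leham is half of the stated objective, so the safety set should treat the two arms alike. Here one route into the set is a dose and the other is control allocation with a visit. The sentence has no brackets, and the term that decides the first route is undefined in a trial where every child is meant to start on the same product.

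The children whose inclusion turns on the wording are those who leave during the first 4 weeks. Under the withdrawal rules, some of them leave because they had an event. An ambiguity that decides whether such children count, possibly in one arm only, should be settled before anyone sees the data by arm.

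**Working it through.** **Inputs.** 200 children randomised 1:1, so about 100 per arm (Abstract, Trial Design). Attrition 20% (Sample Size). First post-baseline visit day 14; common phase ends day 28 (Follow-Up Assessments, Interventions). The safety section gives no figure to reproduce. The timing of attrition, the background event risk and the share tested are not given and are assumed below.

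**Step 1. Who enters under each reading.**

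| Meaning of *study intervention* | Visit condition covers | Study arm needs | Control arm needs |
|---|---|---|---|
| Leham | controls only | a Leham dose, so must stay into week 5 | one visit, first due day 14 |
| Leham | both arms | a Leham dose and a visit | one visit |
| Includes Aravindasava | controls only | one dose | one dose, or one visit |
| Includes Aravindasava | both arms | one dose and a visit | one visit |

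In the first two rows the arms differ in substance. In the last two, dosed children are treated alike, and only undosed controls with a visit are handled differently.

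Usage elsewhere does not settle the meaning. The Introduction calls Aravindasava standard care, and Interventions reserves the label of trial drug for Leham. A separate route for controls also makes most sense if controls are thought not to receive the study intervention. Against that, Table 1 has the trial drug dispensed at baseline, when only Aravindasava is in use.

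**Step 2. Leham meaning: children excluded per 100.** Study arm, leaving before week 5: 20 × 4/16 = 5.0 if attrition is uniform over 16 weeks; 20 × 4/12 = 6.7 if uniform over 12 weeks; 20 if all of it falls in weeks 1-4. Control arm, leaving before day 14: 20 × 2/16 = 2.5, or 20 × 2/12 = 3.3. The net imbalance is 5.0 − 2.5 = 2.5 or 6.7 − 3.3 = 3.3 (rounded) per 100. It is larger if early leavers in the control arm have a final examination that counts as a visit, and up to 20 if all attrition falls between days 14 and 28.

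If every excluded child had left because of an event, 5 events per 100 would vanish from the study arm and 2.5 from the control arm under uniform attrition over 16 weeks. The direction favours Leham to the extent that children left because of events.

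**Step 3. Aravindasava meaning: dilution.** The same 5, 6.7 or 20 per 100 study-arm children are counted without having had Leham. The observed proportion with an event in the Leham period is the true proportion times 0.95, 0.93 or 0.80. With equal early attrition, the control proportion shrinks by the same factor. The risk ratio for that period is then unchanged and the risk difference falls by 5% to 20%.

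**Step 4. Why a comparison from day 28 is worth adding.** Suppose the event rate is constant except for a Leham rate ratio of 2.0 in weeks 5-12. Counted over weeks 0-12, the rate ratio is (4 + 8 × 2)/12 = 1.67; a ratio of 1.5 becomes (4 + 8 × 1.5)/12 = 1.33. With a background risk b per 4 weeks and rate ratio 2.0, the risk ratio is [1 − (1−b)^4]/[1 − (1−b)^2] for weeks 5-12 and [1 − (1−b)^5]/[1 − (1−b)^3] for weeks 0-12:

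| b | Weeks 5-12 | Weeks 0-12 |
|---|---|---|
| 5% | 1.90 | 1.59 |
| 10% | 1.81 | 1.51 |
| 30% | 1.49 | 1.27 |

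**Step 5. Laboratory results.** If 5% to 30% of an arm is tested and 20% of those are abnormal, dividing by the whole arm gives 0.20 × 5% = 1% to 0.20 × 30% = 6%. If 20 per arm were tested with no abnormality, the one-sided 95% upper bound would be 1 − 0.05^(1/20) = 13.9%, so the summary can only be descriptive.

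**The case against.** The best defence is that the sentence is loosely written but harmless. If Aravindasava counts as study intervention, a dosed control enters by the first route exactly as a study-arm child does. If the visit condition covers both routes, it applies to both arms. This stands: a material asymmetry needs the Leham meaning. A reader might infer that the sets differ by arm on any reading, and the text does not support that.

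Three further inferences are tempting and should not be drawn.

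- **That the protocol pools the two phases.** It says neither that they are pooled nor that they are separated. Visits on days 14 and 28 allow a split, which an analysis plan may specify. Step 4 shows only what pooling would do.
- **That the laboratory denominators are wrong.** Disregarding laboratory consent is right for adverse events, and laboratory summaries would normally use children with results. The figures in step 5 arise only if the phrase about all safety analyses is applied literally to laboratory tables.
- **That every effect pushes towards finding no difference.** Steps 2 and 3 rest on opposite meanings of one term and cannot both apply. The first can shift the comparison in Leham's favour; the second shrinks the risk difference.

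It is also fair to say that tabulation by period is ordinary analysis plan content. The entry rule is not, because the article itself fixes it.

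**Conclusion.** The point holds as a badly fixed definition. The entry rule is worded by arm, and its key term is undefined although both arms receive Aravindasava first. Under the Leham meaning, about 5 per 100 study-arm children are excluded, against 2.5 per 100 controls who leave before day 14, with up to 20 per 100 study-arm children if all attrition is early. Under the other meaning, the same 5 to 20 per 100 sit in Leham's denominator without exposure.

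These figures take the planned 20% attrition as given in each arm and assume its timing. The direction in Leham's favour also assumes that some early leavers left because of events, which the withdrawal rules make likely. The size is modest under uniform attrition, but the affected children are among those who matter most for safety.

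**What to change.** 1. Replace the definition with one rule for both arms: all randomised children who took at least one dose of Aravindasava, with no visit requirement, reported by allocated group.
2. Add a Leham safety comparison: adverse events from day 28 onward among children still followed at day 28 in each arm. Because the trial is open-label, show by arm how many left before day 28 and why. Their events remain in the table for the full safety population.
3. Summarise scheduled laboratory results descriptively among children with paired baseline and week 12 samples, and give the number tested by arm.
4. Report clinically triggered tests separately for all children. A paired-sample rule would otherwise drop them in children without a baseline sample.

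The cost is a reworded definition and a few extra table columns. Visit dates and adverse events are already collected. Enrolment is complete, but the article describes the analysis as still to come, so this can be settled and dated before the data are examined by arm.

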### Sample Size

The sample size for the study has been calculated assuming that 60% of participants in the intervention arm and 30% of participants in the control arm will achieve a change in *Z* score of ≥0.5 according to the WHO weight-for-age growth standards. With a 95% CI and 80% power, 42 participants per group need to be enrolled in the trial. After accounting for an attrition rate of 20%, the sample size for the study has been finalized as 50 per group. Therefore, a total of 100 participants per center will be enrolled in the trial.

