**Methods:**

This is a multicenter, open-label, randomized controlled, 2-group pilot study designed to enroll 200 moderately malnourished children, 100 from each participating study center of the Central Council for Research in Ayurvedic Sciences. The children will be screened for moderate malnutrition using the World Health Organization weight-for-age *Z* score through the AnthroCal app developed by the All India Institute of Medical Sciences, New Delhi. After obtaining consent from parents, the participants will be randomized and allocated to 2 groups. The study group will receive *Aravindasava*, 5 mL twice daily after food for 4 weeks, followed by *Ayush BR Leham*, a nutritional supplement, 5 g twice daily before food from weeks 5 to 12. The control group will receive *Aravindasava* for 4 weeks and thereafter receive no intervention for 8 weeks. Both groups will be advised to follow a home-prepared diet during the study period. A follow-up assessment will be conducted after 4 weeks. The primary outcome is a change of ≥0.5 in the World Health Organization weight-for-age *Z* scores, and the secondary outcomes are changes in anthropometric measurements, the frequency of illnesses assessed using a predesigned table, and safety parameters assessed using biochemical measures.

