### Statistical Methods

The primary outcome of the study, namely, the proportion of participants achieving an improvement in the WAZ of ≥0.5, will be analyzed using an intention-to-treat approach. Between-group comparisons for the primary binary outcome will be performed initially using the chi-square test, followed by multivariate logistic regression to estimate adjusted effect sizes after controlling for important covariates, including study center, baseline, WAZ, age, sex, and other clinically relevant variables. This will be done in the following steps:

Step 1: an unadjusted between-group comparison will be performed using the chi-square test to examine the crude difference in the proportion of participants achieving the primary outcome between the intervention and control groups. This provides transparency and allows readers to evaluate the raw effect.Step 2: multivariate logistic regression will be used to estimate the adjusted odds ratio and 95% CI, while controlling for the following prespecified covariates: study center, baseline WAZ (continuous), age (months), sex, baseline nutritional status category, socioeconomic status, and educational status of parents. The adjusted analysis represents the primary analytic result and will be emphasized in reporting and interpretation.

For the secondary outcomes, within-group pre-post changes will be examined using a paired *t* test or Wilcoxon signed-rank test, as appropriate, and will be reported for descriptive purposes. For parameters assessed at multiple follow-up time points, repeated-measures ANOVA or the Friedman test will be applied to assess temporal trends. All analyses will be performed using SPSS (version 29.0; IBM Corp), and statistical significance will be assessed at α=.05 (2-tailed).

Participants who withdraw, are lost to follow-up, or do not complete the week 12 assessment will be documented, and reasons for dropout will be recorded. Dropout rates and reasons will be presented by study group in the CONSORT (Consolidated Standards of Reporting Trials) flowchart.

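### The sample-size paragraph justifies 100 children for the study but enrols 200, so its 80% power does not describe the trial being run

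*Protocol article*

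**What the plan says.** All the sizing statements are in the Sample Size section of the protocol article. The design rates are set by "assuming that 60% of participants in the intervention arm and 30% of participants in the control arm will achieve a change" of at least 0.5 in the weight-for-age Z score. The base size follows: "With a 95% CI and 80% power, 42 participants per group need to be enrolled in the trial". A 20% attrition allowance is then applied, and the section concludes that "the sample size for the study has been finalized as 50 per group. Therefore, a total of 100 participants per center will be enrolled".

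The Methods part of the Abstract gives the total: the trial is "designed to enroll 200 moderately malnourished children, 100 from each participating study center". Study Setting names two institutes, and Trial Design gives 1:1 allocation. The trial therefore has 200 children, 100 per group.

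Statistical Methods describes one between-group comparison of the primary outcome. It starts with a chi-square test. A logistic regression follows, "while controlling for the following prespecified covariates: study center" and several others, and this adjusted result is the primary one. Significance is judged at a two-sided 0.05. The article describes no analysis by center.

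**The concern.** The derivation produces a number for the study, and the closing sentence then applies that number to each center as if it followed. It would follow only if each center were to be powered alone. The article does not say so, and the pooled, center-adjusted comparison points the other way.

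This paragraph is the only justification shown for enrolling 200 children in what the article calls a pilot. Its one power figure also sets how a reader will weigh the result. Someone who takes 80% power for a 30-point difference as the trial's operating characteristic will understate how informative a null result would be. That reader will also not know which difference the enrolled number can detect with 80% power.

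The attrition step adds a second, smaller inconsistency: the stated 50 per group does not leave the required 42 after the stated loss.

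**Working it through.** **Inputs (protocol article).** Response rates p1 = 0.60 and p2 = 0.30, power 80% and attrition 20% (Sample Size); two-sided alpha 0.05 (Statistical Methods); 1:1 allocation (Trial Design); 200 children, 100 per center (Abstract, Methods); two centers (Study Setting, Results).

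**Step 1: reproduce the 42.** The pooled-variance formula without continuity correction is

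n = [1.960·√(2·p̄·(1−p̄)) + 0.842·√(p1(1−p1) + p2(1−p2))]² / (p1−p2)², with p̄ = 0.45.

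- First term: 1.960 × √0.495 = 1.379.
- Second term: 0.842 × √0.45 = 0.565.
- n = (1.944)² / 0.09 = 41.97, so 42 per group.

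The plan's base figure reproduces exactly. Other formulas give 40 (unpooled), 42 (arcsine) and 49 (continuity-corrected).

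**Step 2: the attrition allowance.**
- To keep 42 after 20% loss: 42 / (1 − 0.20) = 52.5, so 53 per group, or 106 children.
- The stated 50 matches 42 × 1.2 = 50.4, rounded down.
- 50 × 0.80 = 40 evaluable per group, two short of 42.

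**Step 3: study size against enrolment.**
- Derived for the study: 2 × 50 = 100 children.
- Enrolled: 2 centers × 100 = 200 children, 100 per group.
- After 20% loss: 100 × 0.80 = 80 per group.

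**Step 4: power of the enrolled trial.** Power = Φ{[(p1−p2)·√n − 1.960·√(2·p̄·(1−p̄))] / √(p1(1−p1) + p2(1−p2))}. For 80 per group this is (0.3 × 8.944 − 1.379) / 0.671 = 1.944, so 97.4%.

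| Situation | Per group | Rates | Power |
|---|---|---|---|
| Plan's base figure | 42 | 60% vs 30% | 80.0% |
| 50 less 20% | 40 | 60% vs 30% | 78.0% |
| Enrolled trial, dropouts counted as failures | 100 | 48% vs 24% | 94.8% |
| Enrolled trial, completers only | 80 | 60% vs 30% | 97.4% |
| Enrolled trial, no loss | 100 | 60% vs 30% | 99.2% |

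The 48% and 24% are 0.8 × 60% and 0.8 × 30%. Exact enumeration of the uncorrected chi-square test gives 97.1% at 80 per group and 99.2% at 100.

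**Step 5: detectable difference.** With 80 per group and a 30% control rate, power reaches 80% at a difference of about 0.216, so roughly 30% against 52%. The planning difference is 30 points.

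**The case against.** The strongest reply is that nothing here harms the trial. The discrepancy makes it larger than calculated, enrolment is complete, and the test, error rate and analysis set are unchanged. The 80% is given as an input to the 42, not as a claim about 200 children. That is fair, and it limits the point to a reporting correction. The derivation still ends in a size that contradicts its premise, and the article gives no other power figure.

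A second reply is that each center may have been sized to stand alone, with the reason in a fuller document. The per-center wording allows this reading, but the article never states it and describes a single comparison with center as a covariate. For the same reason, a reader should not go on to ask how likely both centers are to be significant. No such criterion is set.

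A reader might also infer three stronger criticisms that the article does not support:

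- **The attrition slip leaves the trial short.** It would cost about two points of power in a 100-child trial. With 200 enrolled, 80 per arm remain after 20% loss, well above 42.
- **The doubling is what lets the trial reach significance below its planning effect.** Any trial can do so. At 42 per arm, 22/42 against 13/42 is a 21-point difference and already significant: z = 0.2143 / √(0.4167 × 0.5833 × 2/42) = 1.99.
- **The true power is 97%.** That holds for one unadjusted completer comparison. The plan specifies intention to treat and an adjusted model, so only a range with stated assumptions is supportable.

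**Conclusion.** The concern holds as an inconsistent and unexplained sample-size basis. The derivation supports 100 children as written, or 106 with the attrition step done correctly. The trial enrols 200 and analyses them together. The stated 80% power therefore does not describe it; about 95% to 99% does, depending on how dropouts enter the analysis. With 80 per arm, the difference detectable with 80% power is about 22 points rather than 30.

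These figures rest on the plan's own 60% and 30%, a two-sided 0.05, equal arms, 20% or no loss, and one unadjusted comparison at a single time point. The power of the adjusted logistic model was not computed.

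The attrition error (50 for 53) is real but has no practical effect at the enrolled size. The trial is not underpowered and its validity is not threatened. This should be corrected, but it ranks below the faults that must be resolved before the results can be relied on.

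**What to change.** Change the text of the Sample Size section only:

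- State the enrolled size as 200 children, 100 per arm over two centers, analysed together with center as a covariate, and give the actual reason for 200.
- Replace the 80% as the description of the trial with about 95% to 99% for 60% against 30%, and name the assumption behind each value: dropouts counted as failures, 80 completers per arm, or no loss.
- Add that 80 evaluable per arm give 80% power for about 22 points over a 30% control rate.
- Correct the attrition step to 42 / 0.8 = 53 per group, identified as the requirement for a single comparison with 42 evaluable per group.

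The cost is a few sentences. Enrolment, data collection and analysis do not change. Correcting it before results are reported keeps the explanation from looking retrospective.
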